### Safety measures

All subjective adverse events (41) will be collected from the time of allocation through the last visit (week 24). The investigators are responsible for assessment of the severity and causal relationship of all AEs to study intervention. Documentation on start date and duration of AE, treatment measures taken for the AE will be recorded.

Tolerability will be assessed by proportion of drop-outs due to AEs throughout double-blind period, with lower dropout rates indicate higher tolerability.

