*Rhizoma Gastrodiae*, a kind of traditional Chinese herb medicine, was firstly recorded for treating primary headache in a famous compendium of Chinese medicines called *Sheng Nong's Herbal Classic* in 25 AD to 220 AD. Gastrodin (4-[β-D-glucopyranosyloxy] benzyl alcohol) is the main bioactive constituent of *Rhizoma Gastrodiae* and has been applied clinically as an analgesic to treat migraine and other types of headache for more than 30 years in China (28). Several potential anti-migraine mechanisms of gastrodin have been discovered including inducing a dose-dependent reduction of CGRP- mRNA expression similar to flunarizine (29), preventing the release of CGRP from pre-synaptic central projections, inhibiting the post-synaptic effects of the ERK1/2 downstream signaling pathway to inhibit the firing of second-order trigeminal nociceptive neurons (30), altering acid-evoked membrane excitability of rat dorsal root ganglion neurons and decreasing the amplitude of the depolarization (31). Gastrodin has determined to be safe for use in toxicity studies in animals and occasionally reported adverse drug reactions (ADR) or events (ADE) in clinical practice (32). Recommended dosage of oral gastrodin for treating episodic migraine is 300 mg/day. Although there is no evidence that gastrodin is superior to other analgesics in treating primary headache, low quality evidence obtained from the tremendous amount of case series and observational studies indicates that gastrodin is beneficial for reducing headache frequency and headache intensity with increased dosage. This may largely be explained by the phenomenon that gastrodin is not brain penetrant with a cerebrospinal fluid /plasma ratio of only 5.5% (33). So theoretically, increasing the dosage of gastrodin maybe an ideal option for better efficacy. Previously, the safety of intravenous 40 mg/kg (up to 2,400 mg/day for a 60 kg human) gastrodin had been determined in a clinical trial (34). For efficacy and safety concern, the dosage of oral gastrodin in the present trial will be increased to 600 mg/day.

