### Interventions

All patients will receive full individualized brief intervention (BI) education according to Kristoffersen et al.'s strategy (36) before randomization.

In the gastrodin group, patients will receive gastrodin 600 mg/day (200 mg tid) from baseline to the end of week 12. In the placebo group, matching placebo made of starch will also be prescribed three times a day. If a patient experience unacceptable adverse events as recorded in the instructions for gastrodin such as dry mouth, dizziness and upper abdominal discomfort, the target dose will be tapered down to 300 mg/day.

During the 24-week study period, their usual acute medication intake will be restricted to ≤ 2 days per week. Participants will be asked to return the experimental drug (or placebo) packaging at week 4, and week 8 in the clinic in order to get drugs for the next 4 weeks.

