## Methods: Data collection, management, and analysis

### Data collection methods

Baseline survey and efficacy assessments will be based on information recorded by participants using an eDiary mobile application. Baseline information includes age, educational level (years), any medical history, family history of headache, body mass index, age of headache onset, pre-exiting headache type, monthly headache days, and month medication intake days.

Following variables will be recorded both at baseline survey and each headache attack after randomization: headache characteristics, headache associated symptoms, the headache pain intensity, pain duration of an attack (hours), and acute medication use (type and dosage).

Monthly headache days, month medication intake days, the headache pain intensity, score of HIT-6 and SF-36, treatment failure, drop-outs and any adverse events will be assessed at 4, 8, 12, and 24-week follow-up.

A summary table of eDiary is shown in Table 3. Training for the eDiary will be provided for qualified participants during before randomization.

**Table 3 T3:** Summary of data collection from eDiary.

**Variables recorded**	**Day-28–0**	**At each headache onset after randomization**			
Age	x				
Body mass index	x				
Education years	x				
Age of first headache onset	x				
Any medical history	x				
Family history of headache	x				
Diagnosis of pre-existing headache	x				
Monthly headache days	x				
Month medication intake days	x				
Headache pain characteristics	x	x	x	x	x
Headache associated symptoms	x	x	x	x	x
Headache intensity	x	x	x	x	x
Duration of headache pain (hours)	x	x	x	x	x
Type of acute pain medication intake	x	x	x	x	x
Dosage of acute pain medication intake	x	x	x	x	x

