## Methods: Monitoring

### Data monitoring and harms

An independent data monitoring committee (DMC) will be established to review any spontaneously reported adverse events and identify any safety issues, analyze unintended effects of the study intervention, make recommendations to sponsors, including modification or early termination of the trial when needed. Monitoring on safety trends will be implemented through timely recorded data in eDiary. Other data review on safety issues and pertinent details will be checked by DMC after each visit through source documents. Source documents include a participant's medical records, the eDiary records, and the results of diagnostic tests such as laboratory and neuroimaging tests.

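### Safety measures limits adverse event collection to subjective events, which conflicts with the unqualified wording elsewhere and with the test results and medical records open to the DMC

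*Protocol article*

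**What the plan says.** All references are to the protocol article.

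- **Safety measures**, collection rule: "All subjective adverse events (41) will be collected from the time of allocation through the last visit (week 24").
- **Safety measures**, next sentence: "The investigators are responsible for assessment of the severity and causal relationship of all AEs to study intervention". The qualifier is gone. Tolerability is then measured by the proportion of drop-outs attributed to AEs in the double-blind period, again without a qualifier.
- **Data collection methods**: "treatment failure, drop-outs and any adverse events will be assessed at 4, 8, 12, and 24-week follow-up".
- **Participant timeline and Table 1**: adverse events, unqualified.
- **Data monitoring and harms**: the DMC is set up "to review any spontaneously reported adverse events and identify any safety issues", and also to analyze unintended effects. It follows safety trends through the eDiary and checks other safety details in source documents after each visit. Three types of source document are named: medical records, eDiary records, and "the results of diagnostic tests such as laboratory and neuroimaging tests".
- **Dose**: Background and rationale says "Recommended dosage of oral gastrodin for treating episodic migraine is 300 mg/day"; Interventions says "patients will receive gastrodin 600 mg/day (200 mg tid) from baseline to the end of week 12".

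**The concern.** In ordinary use a subjective event is one the patient feels and reports. A sign found on examination, or an abnormal result from a test done in routine care, is not subjective in that sense. A coordinator who follows the collection rule to the letter could leave such an event out of the AE record. One who follows Data collection methods would enter it. The same event could therefore be counted at one center and not at another.

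The DMC could also see, through source documents, an objective finding that never entered the AE record, so its evidence and the trial's AE tables need not agree.

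This matters because tolerability is half of the stated aim. Its measure, drop-outs due to AEs, depends on what counts as an AE. The trial dose is also above the recommended dose that the article cites, and the Discussion says that practice has no instruction for overdosage. Under-recording of objective events would lean toward the high tolerability that the article anticipates.

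**Working it through.** The point rests on wording, so the check sets the statements side by side. The only arithmetic is the dose comparison.

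**1. What each statement does**

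| Section | Scope of AEs | Role of the statement |
|---|---|---|
| Safety measures, collection sentence | subjective | sets what is collected, from allocation to week 24 |
| Safety measures, next sentence | all AEs | assigns severity and causality assessment |
| Data collection methods | any adverse events | lists assessment times: weeks 4, 8, 12 and 24 |
| Participant timeline; Table 1 | unqualified | visit schedule |
| Data monitoring and harms | spontaneously reported AEs, plus any safety issue | DMC remit |
| Data monitoring and harms | medical records, eDiary records, test results | sources checked after each visit |

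**2. Can these describe one AE set?** Take a clinically significant laboratory abnormality without symptoms, found in a test done for routine care.

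- Collection sentence, read literally: need not be recorded.
- Data collection methods: to be assessed as an adverse event.
- Data monitoring and harms: open to the DMC as a test result or in the medical record.

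The three answers differ, so the scope is not consistent.

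**3. Does the unqualified wording settle it?** Not clearly. The assessment sentence can mean all the AEs just said to be collected, or it can mean every AE. Data collection methods is wider, but it fixes times rather than a definition. The side effects that Interventions names as examples (dry mouth, dizziness, upper abdominal discomfort) are all symptoms, so a site could reasonably take the narrow reading. The other sections support the wide one. The text allows both.

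**4. Dose context.** 200 mg × 3 = 600 mg/day, and 600 / 300 = 2.0. The trial dose is twice the cited recommended oral dose, and that figure is for episodic migraine. The article also reports that "the safety of intravenous 40 mg/kg (up to 2,400 mg/day for a 60 kg human) gastrodin had been determined in a clinical trial" (40 × 60 = 2,400 mg/day), by a different route.

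**5. Size.** The article gives no rate of objective events for gastrodin and no frequency of laboratory or imaging tests. The number of events lost would also depend on which reading each site adopts. None of the three can be taken from the document, so no number is given.

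**The case against.** The strongest reply is that one adjective is being set against several unqualified statements. The article never says that objective events are excluded, and it never says *only*. Investigators assess all AEs, any adverse event is assessed at each visit, and Table 1 simply says adverse events. The word carries a citation whose content is not at hand, so its intended meaning may differ from ordinary use. The DMC is charged with identifying any safety issue and can see records and test results, so objective findings have a route into safety review. The dose has some stated safety background, in the intravenous trial and in animal toxicity studies. Finally, the article condenses a fuller protocol, which may hold the operational AE definition and a laboratory schedule.

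Much of this stands. A reader might infer that objective toxicity at 600 mg/day lies outside the AE set, that no asymptomatic event would be tabulated, or that the DMC judges safety from laboratory and imaging results. The article supports none of these. The wider wording contradicts the first. The second assumes the disputed reading, and an asymptomatic event is seen only if a test is done, whatever the AE definition says. As to the third, test results are one of three source types, alongside reported events and eDiary trends. The lack of a laboratory row in Table 1 is not relied on, because such a schedule may sit in the full protocol.

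The reply does not remove the inconsistency. The limiting word is printed in the one sentence that sets collection, so this is stated text and not detail left to another document. The DMC's access to source documents does not put an event into the AE record or the AE tables.

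**Conclusion.** The concern holds as a contradiction in the scope of AE collection. Safety measures limits collection to subjective events. Data collection methods, Participant timeline and Table 1 do not, and Data monitoring and harms gives the DMC sources that include objective findings. If the collection sentence is followed literally, objective events can be under-recorded and centers can differ.

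This assumes that *subjective* has its ordinary meaning and that at least some sites would act on it. The effect cannot be quantified from the document. Blinded collection by the same rule in both groups gives no reason to expect one group to be recorded differently for the same event. The risk is that objective harms, and any difference between groups in them, are under-reported. The text should be corrected because the contradiction concerns safety data in a trial with a tolerability objective, at twice the cited recommended dose for episodic migraine, and the correction is cheap.

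**What to change.** 1. In Safety measures, replace the opening words of the collection sentence so that it covers: *All adverse events, subjective or objective, including clinically significant findings from any test already performed.* The collection period stays as it is.
2. In Data monitoring and harms, have the DMC review all adverse events collected under Safety measures, not only those reported spontaneously.

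Data collection methods, Participant timeline and Table 1 then agree with the collection rule on scope without further change.

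The cost is two wording changes, slightly more data entry at the sites, and possibly a higher reported AE rate. No new test is required, and the dose, endpoints and sample size are untouched. The change would capture objective findings only where an examination or test has been done; it would not detect abnormalities that nobody looks for.

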**Methods:**

A multicenter, randomized, double-blind, parallel, placebo-controlled trial will be performed. A target sample size of 186 patients who fulfill the International Classification of Headache Disorders 3rd version (ICHD-3) criteria for MOH will be recruited and screened during a baseline screening period of 28 days before being randomly assigned to either the gastrodin or placebo group at a ratio of 1:1. Enrolled patients will be assessed for each 4 weeks during the 12-weeks double-blind phase and followed up at week 24. The primary endpoint is mean change in monthly headache day frequency. Secondary endpoints will be the proportion of remitted MOH, change in headache pain intensity, headache impact test (HIT-6) score, 50% responder rate, treatment failure, monthly acute medication intake days, and Short Form 36-Item Health Survey (SF-36) score. Tolerability will be assessed by drop-out rates though safety monitoring during treatment.

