### Objectives

We will test the hypothesis that gastrodin may serve as a candidate therapy drug during the detoxification phase of MOH with advantages of improving chances of treatment adherence and success. The present study aims to determine the efficacy and tolerability of oral gastrodin as a prophylaxis treatment in MOH.

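### Tolerability counts only adverse-event drop-outs, so patients stepped down from 600 to 300 mg/day for unacceptable adverse events who stay in the trial count as tolerating treatment

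*Protocol article*

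**What the plan says.** The Objectives section of the protocol article states the aim: to "determine the efficacy and tolerability of oral gastrodin as a prophylaxis treatment in MOH". Background and rationale gives 300 mg/day as the recommended oral dose for episodic migraine and then says that "the dosage of oral gastrodin in the present trial will be increased to 600 mg/day".

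Interventions sets the regimen: "patients will receive gastrodin 600 mg/day (200 mg tid) from baseline to the end of week 12". It adds a dose rule. The trigger is "If a patient experience unacceptable adverse events as recorded in the instructions for gastrodin such as dry mouth, dizziness and upper abdominal discomfort", and the consequence is that "the target dose will be tapered down to 300 mg/day". It does not mention withdrawal for this event, and it does not say how the rule applies to placebo.

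Safety measures defines the tolerability endpoint and how to read it: "Tolerability will be assessed by proportion of drop-outs due to AEs throughout double-blind period, with lower dropout rates indicate higher tolerability". The Methods paragraph of the abstract also names only drop-outs: "Tolerability will be assessed by drop-out rates though safety monitoring during treatment".

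Safety measures separately says that "All subjective adverse events (41) will be collected from the time of allocation through the last visit (week 24"), with severity, causality, timing and the action taken for each event. Dose reduction is not named in the tolerability endpoint, in the assessment schedule (Table 1) or among the items to be assessed at visits (Data collection methods).

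**The concern.** The dose rule and the endpoint work on the same patients in opposite directions. The rule is triggered when adverse events become unacceptable, and its effect, where it works, is to keep the patient in the trial. The endpoint registers intolerance only when the patient leaves. A successful step-down thus turns a patient who did not tolerate 600 mg/day into one counted as tolerating treatment.

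This matters because tolerability is in the title and the aim, the trial dose was deliberately raised, and the Discussion expects higher tolerability and plans later dose-effect work. Under the stated reading, a low drop-out proportion would be taken as good tolerability, with nothing in the endpoint to show how many patients were still on the tested dose.

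**Working it through.** The plan gives no tolerability figure to reproduce: no expected rate of unacceptable adverse events, of dose reductions or of adverse-event drop-outs. The power calculation in the Sample size section concerns headache days. The check is therefore one of definitions, followed by an illustration.

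**Step 1. How each kind of patient is scored.**

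| Course over the 12 weeks | Tolerated 600 mg/day? | Tolerability endpoint |
|---|---|---|
| No unacceptable adverse event, stays | Yes | Not counted |
| Unacceptable adverse event, stepped down, stays | No | Not counted |
| Unacceptable adverse event, stepped down, still leaves because of it | No | Counted |
| Leaves because of an adverse event without a step-down | No | Counted |

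The second row is the defect. The last two rows show that masking is partial.

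**Step 2. Size in one arm.** Let I be the share of patients who do not tolerate the full dose, and f the share of those who are kept in the trial on the reduced dose.

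- Endpoint records: I × (1 − f)
- A measure that also counts adverse-event dose reductions records: I
- Understatement: I × f, which is above zero whenever f is above zero

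Input from the protocol: 93 patients per arm (Sample size). I and f are assumptions, shown over a range. Entries are patients out of 93.

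| I | Intolerant, 93 × I | Endpoint, f = 0.5 | f = 0.75 | f = 1 |
|---|---|---|---|---|
| 10% | 9.3 | 4.7 | 2.3 | 0 |
| 20% | 18.6 | 9.3 | 4.7 | 0 |
| 30% | 27.9 | 14.0 | 7.0 | 0 |

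For example, 93 × 0.20 × (1 − 0.5) = 9.3.

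**Step 3. Between-arm difference.** With subscripts G for gastrodin and P for placebo, the endpoint shows I_G(1 − f_G) − I_P(1 − f_P), against a true difference of I_G − I_P. The difference shrinks if I_G × f_G exceeds I_P × f_P and grows if the reverse holds.

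- Same retention in both arms, assumed I_G = 20%, I_P = 5%, f = 0.5: true difference 20 − 5 = 15 points; endpoint 10 − 2.5 = 7.5 points.
- Very unequal retention, same I, f_G = 0.2, f_P = 0.9: endpoint 20 × 0.8 − 5 × 0.1 = 16 − 0.5 = 15.5 points, slightly above the true 15.

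With these values of I, reversal needs f_P to be more than four times f_G (20/5 = 4). Shrinkage is the likelier result, but the documents do not fix it.

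**The case against.** The strongest reply is that the aim concerns oral gastrodin as a prophylactic treatment and is not tied to a fixed 600 mg/day. For a regimen of 600 mg/day with a permitted step-down, drop-out because of adverse events is a coherent measure, since a patient on the reduced dose is following the protocol. This stands in part. It means that the two sections do not contradict each other for the regimen as a whole, and a reader should not infer that the protocol already claims tolerability of 600 mg/day as such. It does not rescue the endpoint as a measure of whether patients can stay on the dose that the trial was set up to test.

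A reader might also infer that the intolerance is lost from the trial. The documents do not support that. Adverse events are collected to week 24 with the action taken, safety is evaluated in everyone who took a dose, and an independent committee reviews the events. Only the tolerability summary leaves the step-downs out.

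A third tempting reading is that the bias must favour gastrodin because lowering a starch placebo cannot relieve anything. Patients and investigators are blinded. A placebo patient whose complaint passes, or who expects relief from a lower dose, may also stay. Masking can therefore occur in both arms.

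Finally, the protocol describes adverse reactions to gastrodin as occasional, so step-downs may be few and the effect small. That is possible. Tolerability also carries no planned power, and the primary endpoint is untouched. Both points limit the weight of the finding without removing it.

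It could be said that tabulating dose reductions belongs in a fuller document. But the article does more than stay silent: it fixes the measure and how it is to be read.

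**Conclusion.** The point holds in a limited form. As defined, the tolerability endpoint counts patients who did not tolerate 600 mg/day but stayed on 300 mg/day as tolerating treatment, and so understates intolerance of the tested dose by I × f. That follows from the two sections alone and needs no assumed rate.

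Its size is unknown, because the documents give neither I nor f. In the illustrated range the endpoint misses from half to all of the intolerant patients, purely because f was set between 0.5 and 1. The direction of the between-arm effect is probable but not established: the difference would shrink if more patients are retained by step-down on gastrodin than on placebo.

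This should be corrected, but it does not threaten the trial. It affects the conclusion on one main aim, not the primary efficacy analysis.

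**What to change.** Reconcile Interventions and Safety measures within the endpoint definition. The dose rule need not change, and no view is taken on it here.

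- Define the tolerability measure as the proportion, by arm, with a dose reduction or a discontinuation due to an adverse event during the 12-week double-blind period.
- Show the two components separately.
- Report by arm the proportion still on the full assigned dose (600 mg/day or matching placebo) at week 12.
- Word any tolerability conclusion as applying to the regimen with permitted step-down, unless these figures support a statement about 600 mg/day.

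The cost is one endpoint definition and a few table rows. The action taken for each adverse event is already to be recorded; the record only has to identify a dose reduction explicitly, in both arms and under the blind. There are two downsides. The tolerability figure may look less favourable, and the composite gives a reduction the same weight as a discontinuation, which is why the components must be displayed separately.
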